### Demographic and clinical characteristics

Data will be collected on age, gender, socioeconomic status, work status, marital status, children, living situation, duration of illness, prior treatment, lowest weight, highest weight, smoking habits, and prior treatment attempts.

### Mini International Neuropsychiatric Interview

The MINI is a short structured psychiatric diagnostic interview for disorders included in the DSM-IV (Diagnostic and Statistical Manual of Mental Disorders, Fourth Edition) and ICD-10 (10th revision of the International Statistical Classification of Diseases and Related Health Problems) [50]. The present study will use the Norwegian version of the MINI (version 6.0.0) [53], which has been validated in clinical settings and has shown satisfactory psychometric properties [54].This Norwegian version of the MINI has not been updated for DSM-5.

### Primary outcome measure

#### Eating Disorder Examination Questionnaire

The EDE-Q [55] is a 28-item self-report instrument designed to measure eating pathology. A recent review systematically studied the psychometric properties of the EDE-Q, and concluded that the instrument is reliable and valid for assessing eating-disorder symptoms [56]. The EDQ-E consists of four subscales: restraint, eating concern, shape concern and weight concern. The summation of the scores on all subscales produce a global EDE-Q score.

We will use a Norwegian translation that has Norwegian norms, good reliability, and expected correlations with BMI in a community sample [57, 58].

### Secondary outcome measures

#### Clinical Impairment Assessment Questionnaire

The CIA is a 16-item self-report questionnaire designed to measure the severity of psychosocial impairment associated with eating disorders. The original version of the scale has been shown to have good reliability, validity, and sensitivity to change [59]. We use a Norwegian translation with Norwegian community norms and which has been shown to be significantly correlated with EDE-Q scores (*r* = 0.83, *p* < 0.01) and BMI (*r* = 0.31, *p* < 0.01) in a community sample [60].

#### Body weight and BMI

BMI will be calculated in the standard manner, as weight in kilograms divided by the square of the height in meters. Weight will be measured using a beam-balance scale and height will be measured using a wall-mounted height board.

#### Beck Depression Inventory

The Beck Depression Inventory-II (BDI-II) is a 21-item self-report inventory designed to measure the degree of depressive symptoms in adolescents (>13 years) and adults [61]. Its psychometrical properties have generally been found to be satisfactory [62]. A recent review found good internal consistency (around 0.9) and good test–retest reliability (ranging from 0.73 to 0.96) [63].

#### Beck Anxiety Inventory

The BAI (Beck Anxiety Inventory) is a 21-item self-report inventory designed to measure the severity of anxiety in adolescents and adults. Its psychometrical properties have been found to be satisfactory, with high internal consistency (α = 0.92) and test–retest reliability [r(81) = 0.75] [64].

#### RAND 36-item Health Survey

The RAND 36-item Health Survey (RAND-36) [65] is a generic multidimensional self-report questionnaire. It consists of 36 questions that assess the 8 health concepts. The 36 questions are also distributed as the Short-Form Health Survey (SF-36) [66] by the Medical Outcomes Trust. The RAND-36/SF-36 is the most widely used measure of health-related quality of life [67]. The RAND-36 has shown satisfactory psychometrical properties [68].

#### The Symptom Checklist-90-Revised

The Symptom Checklist-90-Revised (SCL-90-R) is a 90-item self-report symptom inventory designed to measure psychological symptoms and psychological distress [69].

### Other measures

For a complete overview over all measures in all the different parts of the study, see Table 1.

#### Working Alliance Inventory–Short Form

The WAI-S (Working Alliance Inventory–Short Form) is a 12-item self-report measure of the general alliance in therapy and three different specific aspects of the therapeutic alliance: bonds, goals, and tasks. This measure has both patient and therapist versions, and it has been found to exhibit acceptable validity and interrater reliability [70–72]. This instrument will be administered at 4 weeks into treatment and at the end of treatment.

#### Checklist for dropout interviews

The checklist for dropout interviews will include specific items asking patients whether or not they agree with statements about reasons for ending treatment, including motivation, dislike of the treatment form, being satisfied with their current status, feeling able to continue on their own, not being satisfied with the treatment results, finding the tasks during treatment too difficult, having problems relating to the therapist, having difficulties due to the presence of other illnesses, and having practical problems related to work, studies, family relationships, and finances. The interview will also ask a general question about other reasons, and it will be conducted by a study secretary via telephone within a few weeks of the treatment ending prematurely.

#### Evaluation of early adherence, behavioral changes, and self-monitoring

The CBT-E treatment model includes performing a standardized evaluation of progress at 4 weeks into treatment using the CBT-E stage-2 evaluation form [17]. Different aspects of patient behavioral adherence to treatment are evaluated on the following 3-point scale: not going well, going reasonably well, and going well. The rated behaviors are attending sessions, being on time, self-monitoring, not weighing yourself at home, reading the provided psychoeducational materials, eating regular meals, not eating between meals, and prioritizing treatment.

Each day during CBT-E treatments, the patients complete self-monitoring sheets reporting the times of meals, what they have been eating and drinking, episodes of binge eating and vomiting, and other compensatory strategies. These are reviewed in the sessions with the therapist. In addition, they weigh themselves during the sessions. This constitutes the weekly acquisition of data on BMI, days with regular eating, and numbers of weekly binge-eating and purging episodes.

#### Accelerometers

Physical activity and movement will be measured using wrist-worn accelerometers (AW2 actigraph, Philips/Respironics). The accelerometer will be worn for 7 consecutive days and nights at the following measurement time points: baseline, at the end of treatment, and at 12 months after ending treatment. This device measures both the frequency and magnitude of movement. The use of accelerometers for measuring physical activity and sleep has been validated [73, 74]. During the same period the participants will keep a daily log of their physical activity.

#### The Exercise and Eating Disorders

The Exercise and Eating Disorders questionnaire (EED) [40] is a new self-report questionnaire developed to obtain more-detailed information about exercise regimes and disturbances among patients with eating disorders. This questionnaire focuses on compulsive exercise as a symptom of an eating disorder. The EED consists of 22 items scored on a 6-point scale from 0 (never) to 5 (always). This measure will be applied at the same time points as when accelerometry is performed.

#### Compulsive Exercise Test

The Compulsive Exercise Test (CET) is a self-report questionnaire developed to assess the primary factors influencing the maintenance of excessive exercise. The CET consists of 24 items with 5 subscales: avoidance and rule-driven behavior, weight-control exercise, mood improvement, lack of exercise enjoyment, and exercise rigidity. Preliminary testing for the psychometric properties of the CET has shown promising results [41]. This measure will be applied at the same time points as when accelerometry is performed.

#### Blood samples and biobank

We will obtain a venous blood sample from each patient at five time points, as indicated in Table 1.

Further, we will obtain additional blood samples for later studies of (epi)genetic and other biological markers of interest in AN. Those samples will be stored as whole blood, serum, and on an RNA stabilization medium in a biobank established for the current study. The biobank will be colocalized with an existing biobank (“ADHD in Norway”; the responsible professor is [name], University of Bergen) and using the existing infrastructure for registration, storage, and alarms.

We expect further progress in this field before and during the study, and so there might be changes in the most-suitable analyzing methods for both DNA and RNA and the other biomarkers.

#### Stool samples

Stool samples will be collected from AN patients and healthy controls at four time points. Samples collected at home or in the hospital will be frozen and stored. Several methods are suitable for the characterization of the fecal microbiota. Because of the expected further advances in molecular microbiological approaches the methods will be specified later.

#### Power analyses

All power analyses were conducted with G*Power software (version 3.1.7) [75]. A large effect size is expected for the study treatments (*d* = 0.8). Alpha was set to 0.05 and the power was set to 0.80. The coefficient for the correlation between measurement points was set to 0.50. The results showed that 12 subjects would be needed to detect a significant effect of time. In terms of dropouts, Pr(Y = 1∣X = 1) H0 (which signifies the probability of dropping out when all predictors/covariates are set to their mean values) is set to 0.25. For a two-tailed odds ratio of 2.0, an alpha of 0.05, and a power of 0.80, a sample size of 100 is needed when the R^2^ values of other predictors are set to 0. Linear regression of the treatment outcome with an expected regression coefficient of *d* = 0.20 (two-tailed) and with alpha set to 0.05 and the power set to 0.80 indicated that 81 subjects are needed.

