### Baseline predictors of treatment outcome and dropout, and dropout analysis

High dropout rates have been regarded as a major problem in AN treatment research since they make it difficult to conduct RCTs. This further implies that a relatively large proportion of patients are not able to benefit from current AN treatments. Few previous studies have investigated the characteristics of those patients who do not benefit from AN treatment and their reported reasons for dropping out. Moreover, the predictors of treatment outcome and dropout have to our knowledge not been studied in CBT-E treatment for AN. Such knowledge could act as an important guide for identifying those patients who might need other treatment approaches or how treatments may be improved or tailored for different subgroups of patients.

The rate of treatment dropout is generally reported to vary between 29 % to 73 % in outpatient samples of AN patients [9]. Dropout rates of 36 % and 37 % have been reported for CBT-E treatments of AN [18, 19]. The ANTOP study found dropout rates of 19 % for CBT-E and 34 % for focal dynamic therapy in AN patients [20], suggesting that dropout rates from CBT-E are not higher than those of other treatments for AN, but that they are still significant.

Even though dropout is a major problem with AN treatments in general, and knowledge about the predictors and reasons for dropping out are important in planning and improving interventions, the findings of the few studies investigating this have been ambiguous, and they have mainly focused on personality factors and aspects of the eating disorder [9]. One study examining predictors of dropping out from CBT-E treatment among a mixed group of eating-disorder patients found that treatment dropout was predicted by a history of very low weight, avoidance of affect, and a longer time on waiting lists before starting treatment [22]. Surprisingly few studies have investigated how sociodemographic factors influence treatment outcomes, with one recent review concluding that such data are more or less nonexistent [23].

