### Patient sample

All patients who agree to receive treatment for AN at the SED will be asked to participate in the study. Patients are referred to the clinic by general practitioners and secondary (specialist) health-care services. Written informed consent will be obtained after the patients have received written and oral descriptions about the study. During the past 2 years, 96 AN patients were offered treatment at the SED. We aim to include 100 patients in the current study. Analyses of statistical power showed that the proposed sample sizes in the different studies are sufficient.

The study will include patients aged >16 years who are suffering from AN, as diagnosed based on the DSM-5 (Diagnostic and Statistical Manual of Mental Disorders, Fifth Edition) [1] and confirmed with a clinical examination. Patients offered treatment at the SED have either at least one unsuccessful treatment attempt in a secondary health-care service unit or severe AN that is evaluated as not manageable in a secondary health-care service unit. Participation in the study will be offered to patients younger than 18 years if they do not fulfill the criteria for receiving FBT for AN [49]. Patients will be excluded from participation if it is deemed unsafe to manage them on an outpatient basis or have psychiatric comorbidity (as evaluated with MINI [50]) that precludes a focused eating-disorder treatment, such as psychosis or drug abuse. Patients who are not available to participate during the requested treatment period will also be excluded.

In line with clinical practice, patients will be withdrawn from outpatient treatment if they are unable to participate actively in the treatment program according to the judgement of the clinician, based on not attending sessions (more than three consecutive treatment sessions without giving notice) or not engaging in using the treatment tools (e.g. not self-monitoring).

Treatment at the SED is offered in a stepped care model, whereby patients participating fully in outpatient treatment but still not achieving the necessary changes will be offered a more-intensive treatment option (Intensive CBT-E) as inpatients or in day care. These patients will be included as a separate group in the analyses.

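### The regression sample size of 81 does not follow from the stated coefficient of 0.20: as a standardised coefficient, 0.20 needs about 191 patients

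*Protocol article*

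**What the plan says.** The Power analyses section reports three calculations: the change over time, the predictors of dropout, and the predictors of treatment outcome. The third is at issue. It reads "Linear regression of the treatment outcome with an expected regression coefficient of" d = 0.20, and continues "two-tailed) and with alpha set to 0.05 and the power set to 0.80 indicated that 81 subjects are needed". The section names the software ("All power analyses were conducted with G*Power software (version 3.1.7"). It does not give the scale of the 0.20, the number of predictors in the model, or any allowance for missing outcomes.

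The Patient sample section sets the enrolment target ("We aim to include 100 patients in the current study") and concludes: "Analyses of statistical power showed that the proposed sample sizes in the different studies are sufficient".

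Research question 2 lists 12 baseline factors and asks whether they predict outcome or dropout. Research questions 3 and 5 ask the same kind of question about early change, alliance and physical activity.

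**The concern.** The sentence prints an effect, a sidedness, an alpha, a power and a resulting N, so it can be checked, and the pieces do not fit. The label is also wrong: d measures a standardised mean difference and is not a regression coefficient. This is not detail that an article may leave to a fuller document, since both the input and the result are printed.

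The outcome parts of research questions 2, 3 and 5 rest on this calculation. If the effect of interest really is a standardised coefficient of 0.20, the study has about an even chance of missing each such predictor, while the reader is told that the sample is sufficient. A non-significant predictor could then be given more weight than it can bear.

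**Working it through.** **Inputs.** Effect 0.20, two-tailed alpha 0.05, power 0.80 and N = 81 come from Power analyses. Enrolment of 100 comes from Patient sample. The number of predictors is not stated in the power section; the 12 factors are counted from research question 2.

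**Formulas.** For one coefficient, two-sided, the test is a noncentral t with noncentrality √(f²·N) and N − k − 1 degrees of freedom, where k is the number of predictors. For the overall test it is a noncentral F with noncentrality f²·N. Conversions: f² = r²/(1 − r²) for a correlation or standardised coefficient with one predictor; f² = R²/(1 − R²) for the overall test; r = d/√(d² + 4) for Cohen's d. Single-coefficient results below use k = 1; at N = 81, using k = 12 changes power by less than 0.2 percentage points.

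**Trying to reproduce 81 from 0.20 (80% power, two-sided, one coefficient).**

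| Reading of 0.20 | f² | N needed |
|---|---|---|
| Standardised coefficient or correlation | 0.04/0.96 = 0.0417 | 191 |
| Cohen's f | 0.20² = 0.04 | 199 |
| f² itself | 0.20 | 42 |
| Cohen's d, so r = 0.20/√4.04 = 0.0995 | 0.01 | 787 |

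A Fisher z calculation for r = 0.20 gives 194, close to 191. Using a one-sided test does not rescue the figure: the first three rows become 150, 156 and 33.

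**What does give 81.**

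- One coefficient, two-sided, f² = 0.10: power is 79.8% at N = 80 and 80.3% at N = 81, so N = 81. The partial r is √(0.10/1.10) = 0.30.
- Overall F test, R² = 0.20 (f² = 0.20/0.80 = 0.25), 12 predictors: power is 79.7% at N = 80 and 80.4% at N = 81, so N = 81.
- An unstandardised slope of 0.20, if SD(x)/SD(y) = 0.3015/0.20 = 1.51. No SDs are given.

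An overall F test with f² = 0.20 and 7 predictors comes close, at N = 80.

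**Power under the candidate readings.**

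| Effect | N = 81 | N = 100 |
|---|---|---|
| Standardised coefficient 0.20 | 44% | 52% |
| f² = 0.10, one coefficient | 80% | 88% |
| R² = 0.20, 12 predictors, overall F | 80% | 91% |
| f² = 0.20, one coefficient | 98% | 99% |

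The smallest correlation detectable with 80% power is 0.30 at N = 81 and 0.27 at N = 100.

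**Attrition, as an assumption only.** Suppose that every patient who drops out of treatment has no outcome record. The section on baseline predictors cites CBT-E dropout of 36% and 37% ("Dropout rates of 36 % and 37 % have been reported for CBT-E treatments of AN") and 19% in a German randomised comparison. The dropout power analysis uses 25%.

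| Dropout | Left of 100 | Power at f² = 0.10 |
|---|---|---|
| 19% | 81 | 80% |
| 25% | 75 | 77% |
| 36–37% | 64–63 | 70% |

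**The case against.** The strongest defence is that 0.20 is a mislabelled R². Research question 2 lists exactly 12 baseline factors, and R² = 0.20 with 12 predictors gives 81. With 100 patients that test has 91% power. This is a plausible origin of the number, and it is why one cannot say that the calculation actually run was underpowered. It does not save the sentence as printed. The text describes a two-tailed test of a coefficient; an overall F test is neither, and it shows only that the set of predictors explains something, whereas the research question names individual factors. The unstandardised slope cannot be excluded either, but it needs an SD ratio that appears nowhere.

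A reader might go further and infer that the plan's own 25% dropout leaves 75 patients, below 81, so that 80% power is lost. The documents do not support this. The 25% is an input to the logistic analysis of dropout: "which signifies the probability of dropping out when all predictors/covariates are set to their mean values) is set to 0.25". It is not an allowance for missing outcomes. The Discussion treats leaving the study and leaving treatment as separate events, and Table 1 schedules a status item that includes having dropped out at the later assessments. At the cited 19%, exactly 81 would remain. Nor can patients who move to intensive CBT-E be subtracted: Patient sample says that they form a separate group in the analyses, not that they leave the predictor regressions.

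It is also fair to say that the pre-post question is powered separately and is untouched by this point.

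**Conclusion.** The point holds as a mismatch between a printed input and a printed result. On each scale tried for a single coefficient (standardised coefficient, f, f² or d), 0.20 gives an N from 42 to 787 and not 81; the one exception needs SDs that the article does not state. If 0.20 is a standardised coefficient, the required N is about 2.4 times the stated one (191/81), and power at full enrolment is about 52% instead of 80%, with no dropout at all. If the intended effect was f² = 0.10, then 81 is right and 0.20 is wrong. The article does not allow a choice between these, so an unconditional statement that the study lacks 80% power would go too far. What can be said is that the sufficiency claim is not supported, for these regressions, by the calculation offered. Attrition would matter only if treatment dropouts lack outcome data; on the f² = 0.10 reading it would then cost between nothing and about 10 percentage points of power.

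**What to change.** In Power analyses, correct either the effect size or the N so that they agree, and state the effect measure, the test and the number of predictors. If f² = 0.10 was the input, suitable wording would be: *With 81 subjects, a single predictor with f² = 0.10 (partial r about 0.30) is detected with 80% power (two-sided alpha 0.05). With 100 subjects the smallest correlation detectable with 80% power is about 0.27, and power for a standardised coefficient of 0.20 is about 52%.* If the overall F test was used, say so, drop the reference to two tails, and add that individual predictors are not powered by it.

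In Patient sample, limit the sufficiency statement to the effects that are powered.

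Add one sentence on outcome data after treatment dropout: either that such patients are still assessed, or an assumed loss with its range, for example 19% to 37%, and the resulting power. Do not fix 75 evaluable patients as a design figure.

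The cost is the rewording of a few sentences and a less favourable stated figure. No extra patients and no change to the design are needed.

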#### Study setting

The SED is a regional unit for the most severely ill eating-disorder patients in Western Norway. This unit serves a population of 1 million inhabitants. Since 2007, all therapists at the SED have contributed to comprehensive data collection as part of internal quality control. As a follow-up and extension of this work, a Regional Research Database (Western Norway) for eating disorders has been designed, which is located at the SED. This database has been approved by the Norwegian Data Inspectorate, and data collection was commenced in January 2016. The present study will use data from this database in addition to measures specifically added to test the hypotheses of this study. The present study has been designed in close collaboration with the therapists at the SED in order to ensure that it will be possible for them to perform the data collection. The process assessments included in the present study are already embedded in the clinic and are applied in clinical practice.

## Discussion

Conducting studies in an ordinary health care setting poses both challenges and advantages. An advantage is the possibility to test how treatments evaluated in research clinics translate into an ordinary public hospital setting.

A challenge when implementing studies in an ordinary clinical setting is to secure the quality of the data collection and avoid missing data. The therapists have a busy schedule and assessments for the study need to be embedded into their daily routines and be experienced as meaningful for both therapists and patients. To secure this a detailed protocol for the data collection is written in co-operation with the therapists. Further, the therapists have been involved in designing the study through several meetings.

At 12-months follow-up the participants in the treatment study are compensated for their travel expenses for coming to the clinic to avoid this being a barrier for participating. The healthy weight controls likewise get their expenses covered as well as receiving a reward of 500 NOK (about 40 Euros).

Another aspect of implementing a treatment study into clinical practice is the question of patients receiving different treatments based on entering the study or not; and the need to follow national clinical guidelines for treatment. This makes a randomized controlled trial difficult to conduct in this setting. A waitlist condition also would prove ethically difficult because of the severity of the illness. Accordingly, in this study all patients receive the same treatment irrespective of study participation and there is no waiting-list or comparison group for the treatment condition. This constitutes a weakness when drawing conclusions based on treatment response.

To secure patient safety in cases of withdrawing from the study the routines are as follows: For patients deciding to leave the study, treatment continues. If the patient decides to end treatment pre-maturely they are referred back to their primary GP or to other relevant treatment. There is always an invitation to return to the eating disorder treatment at a later point of time if this is relevant and the patient wants to work in treatment again.

The longitudinal design of this study and the inclusion of a healthy control group are significant strengths that will contribute to a better understanding of AN pathophysiology, which could have implications for treatment efficacy.

